##### Sample size

The effectiveness of the HATHI intervention will be assessed at 6 months using PEth as the primary outcome. A total sample size of 450 participants provides 80% power at a 5% significance level to detect a minimum mean difference of 90 ng/mL between randomized arms. This calculation assumes a mean PEth of 212 ng/mL (SD = 205 ng/mL), as observed in the ongoing HATHI study. Calculations assume a 10% loss to follow-up, and intra-class correlation coefficient of 0.04 to account for site-counsellor clustering.

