##### Randomization procedures: Sequence generation and allocation concealment

Eligible participants will be randomized in a 1:1 ratio upon completion of the baseline evaluation. The study biostatistician, independent of the trial will generate the randomization sequence in permuted blocks with block size 4, and randomization will be stratified by the presence of TB only; HIV only; and TB/HIV co-infection. Allocation will be concealed using sequentially numbered, opaque, sealed envelopes. The study counselor will enroll and assign participants to the interventions

By nature of the interventions being tested, this will be an open-label trial in which neither the subjects, study coordinators, nor interventionists will be blinded to treatment assignment after randomization. However, to decrease potential sources of bias, research assistants, staff abstracting medical records, and data analysts will all be blinded to treatment arm of individual patients.

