#### Aim 2: Intervention effect on TB and HIV clinical outcomes

Composite TB treatment outcomes will be summarized as rates within each intervention arm. Adjusted differences in composite TB outcome rates between intervention arms will be estimated using multivariable Poisson regression models with random effects for study site and counsellor. All-cause mortality over the 12-month follow-up period will be assessed using time-to-event methods. The cumulative mortality function will be estimated using the Kaplan–Meier product-limit estimator, stratified by intervention arm and accounting for clustering by study site and counsellor. Adjusted differences in mortality risk between intervention arms will be estimated using multivariable Cox proportional hazards regression models incorporating random effects for study site and counsellor. Similar survival analysis methods will be applied to evaluate time to sputum-culture conversion among participants with microbiologically confirmed TB.

Differences in HIV-related outcomes, including viral suppression and antiretroviral therapy adherence, will be evaluated using adjusted multivariable logistic regression models, with appropriate specification of random effects and covariates.

Although the study is not explicitly powered to detect differences within individual disease subgroups, all analyses will be conducted stratified by disease cohort, including TB-only, HIV-only, and TB–HIV co-infected participants. This stratified analytic approach will allow for an assessment of the consistency of the BI intervention’s effectiveness across clinically relevant populations. Findings from these subgroup-specific analyses will be interpreted cautiously and considered exploratory in nature. The results are expected to inform hypotheses regarding differential effects and to identify potential gaps requiring targeted investigation in future, adequately powered studies.

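### Consistency across the TB-only, HIV-only and TB/HIV cohorts is to be assessed from cohort-stratified analyses, with no direct comparison of the cohort effects planned

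*Protocol article*

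**What the plan says.** The last paragraph of the section on Aim 2 (intervention effect on TB and HIV clinical outcomes) states that "all analyses will be conducted stratified by disease cohort", naming the three disease groups. It gives the purpose directly afterwards: "This stratified analytic approach will allow for an assessment of the consistency" of the intervention's effectiveness across these populations. The same paragraph concedes that the trial is not powered within cohorts. It calls the results exploratory, asks for caution, and expects them to suggest hypotheses about differential effects for later trials.

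Cohort is also a design factor. In the randomisation section, "randomization will be stratified by the presence of TB only; HIV only; and TB/HIV co-infection". The primary model under Aim 1 is a univariable regression on arm with random effects for site and counsellor, so cohort does not enter it. No part of the article names an arm-by-cohort interaction, a heterogeneity test or an estimated difference between cohort effects.

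In the Sample size section, "A total sample size of 450 participants provides 80% power at a 5% significance level"; the target is a 90 ng/mL difference in mean PEth. Current cohort sizes are not given. The amendments section says only that the HIV-only group was added within the same total of 450, and that TB/HIV recruitment had been low.

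**The concern.** Consistency is a statement about the differences between cohort effects. An analysis within one cohort compares that cohort's effect with zero. Three such analyses side by side do not address the differences unless they are then compared, and the article does not say how that would be done.

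The gap matters because the cohorts are small relative to the trial. The natural shortcut is to note which cohorts reach significance, and with low power in each cohort that pattern is mostly noise. Since the results are meant to suggest hypotheses about differential effects, a chance pattern could steer later work towards one disease group and away from another.

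**Working it through.** **Inputs.** From Sample size: N = 450, 80% power, 5% significance (taken as two-sided), difference 90 ng/mL, SD 205 ng/mL, and "10% loss to follow-up, and intra-class correlation coefficient of 0.04 to account for site-counsellor clustering". From the randomisation section: 1:1 allocation and three strata. Assumed: the cohort splits, and the same effect and SD in every cohort.

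**1. The plan's own figure.** Without clustering, n per arm = 2 × (205 × 2.80 / 90)² = 81.4, so 82 per arm, 164 in total, and 183 after 10% loss. With N = 450 there are 405 evaluable, or 202.5 per arm, so the implied design effect is 202.5 / 81.4 = 2.49. Solving 1 + (m − 1) × 0.04 = 2.49 gives m of about 38 per cluster (m = 38 returns N = 449). The 450 therefore reproduces only with a cluster size that the article does not state. Below I take the stated 80% power as given.

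**2. Power in each cohort.** 80% power means an expected overall z of 1.96 + 0.84 = 2.80. With the same effect everywhere, a cohort of n has expected z = 2.80 × √(n/450) and power Φ(z − 1.96). For n = 200, z = 1.87 and power is 46%. For n = 50, z = 0.93 and power is 15%.

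**3. Pattern of significance under an identical effect.** The cohorts contain different people, so the chances that all or none are significant are taken as products of the cohort powers (or their complements). Mixed = 1 − all − none.

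| Assumed split | Power by cohort | All significant | None | Mixed |
|---|---|---|---|---|
| 150/150/150 | 37/37/37% | 4.9% | 25.5% | 70% |
| 200/200/50 | 46/46/15% | 3.3% | 24.4% | 72% |
| 250/150/50 | 55/37/15% | 3.1% | 24.1% | 73% |
| 250/100/100 | 55/26/26% | 3.8% | 24.5% | 72% |

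**4. Sensitivity.** If clustering weighs less within cohorts, or not at all, the mixed share at 90 ng/mL runs from 60% (equal cohorts, no clustering) to 88% (a very uneven split, no clustering). With a true effect of 60 ng/mL, equal cohorts and the full design effect, it falls to 46%, because in 53% of trials no cohort is significant.

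**5. Other ways of reading the same results (simulation, identical effect).** If 95% intervals are compared, some pair of cohort intervals fails to overlap in about 2% of trials. If only point estimates are compared, the largest is at least twice the smallest in 71–84% of trials with the full design effect, and in 46% in the most favourable case. A heterogeneity test on 2 degrees of freedom rejects in 5%, as it should.

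**6. What an interaction test can detect.** Suppose one cohort, holding a share f of participants, has no effect and the other two have 90 ng/mL. The non-centrality is 2.80² × f(1 − f).
- f = 50/450: 7.85 × 0.111 × 0.889 = 0.78, power about 11%.
- f = 150/450: 7.85 × 0.333 × 0.667 = 1.74, power about 20%.
- f = 200/450: 7.85 × 0.444 × 0.556 = 1.94, power about 22%.

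**7. Width of the intervals.** The standard error of a cohort effect is 90/z: 90/1.87 = 48 ng/mL for n = 200 and 90/0.934 = 96 for n = 50. The difference between those two effects has standard error √(48² + 96²), about 108, so its 95% interval is roughly ±211 ng/mL.

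**The case against.** The strongest reply is that the 70% tests a rule the protocol does not contain. Nothing in the Aim 2 section says that consistency will be read from significance, and step 5 shows that comparing intervals would rarely suggest a conflict. This stands. A reader might infer that the planned analysis will usually make the cohorts look inconsistent. The document does not support that, because the result depends on how the cohort results are read.

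A second reply is that stratified estimates are not useless for the question. Cohort estimates with their standard errors are enough for an approximate heterogeneity test, so it would be wrong to say that separate analyses cannot show consistency or difference. This also stands. Nor does the article give the form of the cohort analyses, so criticism of how variance components would be estimated in small cohorts would be conjecture.

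Third, the paragraph already admits low power and calls the results exploratory, and suggesting hypotheses for later trials is a proper use of exploratory subgroups. That limits the harm, but it does not supply the missing comparison.

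Fourth, an interaction test is weak here (step 6), so resting claims of consistency on it would invite the opposite error: a cohort with no effect would escape detection in roughly 80–90% of trials. This is correct and shapes the fix.

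Finally, the formal contrast might sit in an analysis plan that is not shown. But the article itself names the stratified approach as the means of assessing consistency, so the point concerns what it states and not only what it leaves out.

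**Conclusion.** The point holds in a limited form and is minor. The article relies on cohort-stratified analyses to assess consistency and plans no direct comparison of the cohort effects. Read by significance, an identical effect would give a mixed picture in about 70% of trials (70–73% over the four splits in the table). That figure rests on 80% overall power, the same effect and SD in each cohort, assumed cohort sizes, and an outcome shared by all three cohorts. It is built on the PEth calculation and does not carry over to TB-specific or HIV-specific outcomes, which involve two cohorts each. The article does not state the significance rule, and estimates read with intervals soften the problem. The primary comparison of PEth at 6 months is not affected.

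**What to change.** For each outcome, fit one model on all applicable participants with arm, cohort and arm-by-cohort terms, keeping the planned random effects. That means three cohorts for alcohol outcomes and all-cause mortality, and two for TB-specific or HIV-specific outcomes. From that model report the cohort-specific effects and the between-cohort differences in effect, each with a confidence interval, and the interaction test.

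Add three statements to the Aim 2 section:
- Neither consistency nor difference will be inferred from cohort-specific p-values.
- The interaction test has low power, about 11–22% if one cohort has no effect, under the assumptions above.
- A non-significant interaction does not establish consistency.

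Keep the exploratory label. Cohort is already a randomisation stratum, so no new data are needed. The cost is one added model term, a few sentences, and wide intervals that will show how little the trial can say about differences between cohorts.

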#### Aim 3: RE-AIM analyses

Descriptive analyses of quantitative data will be used to investigate the RE-AIM dimensions across stakeholder levels, characterizing the median and distribution of scores. The qualitative data will provide context to the quantitative data and in-depth understanding of barriers and facilitators to program implementation in the local context. Transcripts will be analyzed in an iterative fashion, and concurrent with on-going interviews to allow data to inform queries in subsequent interviews. We will use both deductive and inductive coding for qualitative analysis, deriving codes from the interview guide based on RE-AIM dimensions in addition to identifying emergent themes. Qualitative interviews will be coded by two study team members. The research team will examine these provisional codebooks and create a representative codebook for use in the entire analysis. Inconsistencies will be examined and resolved through consensus. We will merge and integrate quantitative and qualitative data. The qualitative themes will be compared to survey results, combined and jointly displayed to enhance data interpretation.(69, 70).

#### Aim 4: Cost and cost-effectiveness analysis

Cost of the HATHI intervention will be assessed using activity-based costing framework and ingredients approach where resource use and cost data will be assessed based on key HATHI intervention activities. Fixed costs (e.g., HATHI implementation costs) and resources common across multiple intervention activities will be apportion to each activity based on the distribution of direct human resource time committed to each intervention activities. All costs will be assessed in both local (Indian Rupees) and study year United States (US) dollars, with capital assets and fixed costs annuitized using 3% discount rate (varied between 0 and 10% in sensitivity analyses) and relevant expected useful life years.

For patient cost analysis, we will assess the number and percentage of patients avoiding catastrophic cost due to TB as a result of the intervention relative to the control arm. Catastrophic cost will be defined as TB-related patient-incurred cumulative total costs during the observational period exceeding 20% of patients’ annual household income.(71) We will examine the association between catastrophic costs and AE (e.g., treatment failure) using univariable and multivariable analyses generating odds ratios for each variable as risk factor to the catastrophic costs. This will be assessed independently for each study arm and repeated as a combined analysis for difference in proportion of participants experiencing catastrophic costs between the two study arms.

Cost-effectiveness of the intervention will be assessed based on ‘net benefits’ or net-monetary benefits approach,(72) where we will calculate incremental health systems costs per one additional patient successfully completing TB treatment and bench mark this metric against a range of willingness to pay thresholds, starting with the India’s GPD per capital for our analytic year. We will conduct additional analyses on key effectiveness outcomes – incremental cost per participant achieving alcohol reduction and per quality adjusted life years gained – to examine the relationships in the cost-effectiveness outcomes and conclusions across different effectiveness measures.

### Methods in analysis to handle protocol non-adherence and any statistical methods to handle missing data

The sample size calculation incorporates a 10% allowance for loss to follow-up or missing data at the 6-month primary endpoint to preserve 80% statistical power. Given the high rates of attrition typically observed in alcohol intervention trials, we will assess the mechanism of missingness (missing completely at random, missing at random, missing not at random), acknowledging that this is rarely verifiable in practice. Missing data will be addressed using four approaches: last observation carried forward, worst-case scenario imputation (classifying all missing as heavy drinking & using upper limit of PEth detection), multiple imputation with chained equations, and full information maximum likelihood estimation. Auxiliary variables (baseline alcohol use measures, age, TLFB, AUDIT, etc.) will be included in the latter two methods, and sensitivity analyses will be performed across all approaches to evaluate robustness.

### Monitoring

Safety and oversight of the study will be provided by the principal investigators (GC, AG) and the study team in India (NS, AK, RB) and associated Institutional Review Boards (IRB) at BJGMC and DYPMC, 2) a Data Safety and Monitoring Board (DSMB), and 3) the Johns Hopkins Medical Institution’s IRB.

We have established a DSMB consisting of an epidemiologist/physician who implements clinical trials for infectious diseases in India; a clinical psychologist with expertise in alcohol use disorders, alcohol measurement, alcohol clinical trials and behavioral interventions; and a biostatistician. The DSMB is independent of the sponsor and the investigators without competing interests. The DSMB will meet annually and adhoc. There will be no planned interim analyses.

#### Composition of the coordinating center and trial steering committee

The trial will be coordinated through Johns Hopkins University and Johns Hopkins India in partnership with the two Indian clinical sites and investigators at the London School of Hygiene and Tropical Health and University of Washington. The data coordinating center is based in Pune, India and managed by Johns Hopkins India. The coordinating center comprises of experienced trialists, behavioral scientists, study managers, biostatisticians and data managers. The study team, including the PIs and site coordinators, meet every two weeks and review study conduct and recruitment and retention milestones.

#### Harms

At baseline and each follow up visit, participants will receive the CIWA to assess for alcohol withdrawal and they will be asked about withdrawal symptoms. Participants with withdrawal symptoms are referred directly to psychiatry for further evaluation and treatment.

At follow-up visits, all participants will be asked about urgent care/emergency department visits, hospitalizations and reasons for these. All AEs and SAEs are reported to the principal investigators (PI), local medical co-investigators and the local IRBs. Site PIs will be responsible for reporting the SAE to the IRBs of BJGMC and DYPMC for review at respective sites. Any SAE including death or life-threatening condition occurring in the study will be reported to Ethics Committee within 24 hours of site awareness as per Indian National regulatory guidelines and annually to the Johns Hopkins IRB and NIH (if not study related). Any lab values of grade 3 or above per DAIDS AE Grading Table, Corrected Version 2.1, dated July 2017 will be reviewed and reported. SAEs that are deemed to have a probable or definite relationship to study procedures will be promptly reported to study site PIs and to overall PIs who will report to the local IRBs, Johns Hopkins IRB and the NIAAA project officers. In addition, reports will be submitted to the IRBs as part of the annual renewal process and the DSMB, summarizing all AE and SAE and how they were addressed by the study team.

#### Auditing

No independent agency or person will perform an audit. Quality assurance activities are performed by a designated quality assurance officer biannually.

### Ethics and dissemination

#### Protocol amendments

Protocol amendments are reported to the local IRBs, the data monitoring committee and the sponsor. Amendments are also updated in clinical trials.gov.

The following protocol amendments have occurred during the course of this study. We obtained a supplement from the National Institute on Alcohol Abuse and Alcoholism (NIAAA) to add collection and storage of plasma, urine and stool in 2023. We obtained a second supplement from NIAAA in 2024 to add an HIV only arm. The original protocol sought to recruit 450 individuals with TB (n=300) and HIV and TB co-infection (n=150) with unhealthy alcohol use. From the time of grant inception to implementation, HIV and TB co-infection incidence declined due to effective ART. Given lower recruitment of persons with HIV and TB co-infection, we added an HIV only arm, consisting of PWH with unhealthy alcohol use, with the same overall recruitment goal of 450 people. Finally, we changed the primary outcome of the study from self-reported drinking days and heavy drinking days using the TLFB to the alcohol biomarker PEth as recommended by the DSMB on May 30, 2024, due to underreporting alcohol by self-report.

#### Informed Consent Procedure

The informed consent process will be done in person in a private room conducted by study counselors. Study procedures, risk and benefits will be discussed in the local language of choice (Marathi, Hindi and English). The informed consent form includes a description of each of the study visits including survey assessments and biological sample collection; randomization and study condition procedures; remuneration; risks and benefits confidentiality; rights of the participants. Prior to signing the consent form study comprehension will be assessed by a study counselor and participants will be given time to ask any questions they have about the study. While we anticipate the consent process to take 30 minutes, as much time as necessary will be allowed for the consent.

#### Confidentiality

Personal information will be collected for participant tracking purposes and medical record abstraction. We will create unique study IDs for all participants and use these study IDs for all data forms for computer entry and storage. We will report study findings in aggregate only. In addition, all study data are stored in REDCap, which is located on a secure JHU server. All informed consents (PHI) will be stored in the DYPMC and BJGMC data center under double lock and key and only the study team will have access to these files.

## Discussion

Unhealthy alcohol use is a known risk factor for both HIV and Tuberculosis infection acquisition and for poorer HIV and TB treatment outcomes. HATHI,- **H**ybrid trial for **A**lcohol reduction among people with **T**B and **H**IV in **I**ndia, is to our knowledge one of the first hybrid effectiveness-implementation studies testing the effectiveness of an evidence-based behavioral alcohol reduction intervention integrated into TB and HIV clinical care in India. As such, this study will generate new knowledge that will inform delivery of alcohol counseling among people with TB and HIV in these clinical settings

Strengths to this study include the intentional selection of the hybrid design, that allows for the rigor of a randomized controlled trial and the collection of implementation barriers and facilitators of alcohol intervention integration into these clinical settings. Additional strengths include selection of an evidence-based intervention with core components effective in HIV clinical settings and in Indian primary care clinics that has been culturally adapted for people with HIV and TB in India and rigorous quality and fidelity monitoring of behavioral counseling sessions. Finally, use of an alcohol biomarker, PEth, as our primary outcome will overcome challenges of underreported alcohol use due to social desirability.

Despite these strengths, there have been challenges to trial implementation. Specifically, low self-report of alcohol use on the TLFB interview, in contrast to the AUDIT and PEth was noted, resulting in DSMB recommendation to change the primary outcome from self-report to biomarker. Moreover, enrollment of women in the study has been limited, which is likely attributable to the lower prevalence of alcohol use among women in India and potential under-reporting due to the low social acceptability of alcohol use among women in this context. Finally, we have experienced interruptions in recruitment of people with TB at various timepoints in the study due to lack of TB medication availability resulting in reduced screening (April-June 2024) and a TB health staff strike (February 11, 2024-March 5, 2024, and August 18-September 17, 2024).

Notwithstanding these limitations, HATHI will generate new knowledge that will inform delivery of alcohol counseling among people with TB and HIV in these clinical settings. Further, the hybrid design will allow for qualitative exploration of implementation challenges which will directly inform intervention reach and hasten scale up of the intervention should it be effective.

